## Abstract

**Introduction:**

The COVID-19 pandemic has led to unprecedented strain to healthcare systems worldwide and posed unique challenges to the healthcare professionals (HCPs) and the general public.

**Objectives:**

The aim of this study is to evaluate the impact of COVID-19 on the mental health, behavioral, and physical wellbeing of HCPs in the early and mid-term periods of the pandemic in comparison to non-HCPs. Thus, facilitating and guiding optimum planning and delivery of support to HCPs.

**Methods and Analysis:**

An observational cross-sectional survey and cohort study aiming to enroll over 1050 participants (minimum, 800 HCPs and 250 controls). Study questionnaires will be completed at baseline and after 6-weeks and 4-months. Recruitment initiated July 2020. The study was designed in London, United Kingdom, but open to participants worldwide. Baseline: Questionnaires comprising of validated self-administered screening tools for depression, anxiety, sleep-related issues, wellbeing, and burnout. The questionnaires also explore changes in behavior and physical wellbeing of the participants. In addition, associations of these mental health and behavioral factors with work-related factors and support will be explored. Six-weeks and 4-months follow-up: Follow-up questionnaires will assess change in symptoms of anxiety and depression, sleep disorders, use of alcohol and other substances, behavioral or interpersonal relationship changes. Physical wellbeing will be assessed through the presence of suspected or confirmed COVID-19 infection and absence from work. We will also evaluate the impact of variable provision of personal protection equipment (supply and training), extended working hours, and concern for the wellbeing of family members, anxiety levels, and evidence of burnout.

**Statistical Considerations:**

The study has 80% power to detect a 10% difference of combined depression and/or anxiety symptoms between the groups using two-sided type 1 error at 0.05 at baseline. Assuming that only 50% of these HCPs agree to be a part of a cohort survey, we will have 80% power to detect around 12% difference in the two groups in reported physical symptoms (20% vs. 32.3%), or prevalence of depression and/or anxiety at the end of the study.

**Ethics:**

The study was approved by the Cambridge East, Research Ethics Committee (20/EE/0166).

**Trial Registration Number:**

ClinicalTrials.gov, NCT04433260.

## Introduction

The United Kingdom and the rest of the world now face a pandemic caused by a novel coronavirus, severe acute respiratory syndrome coronavirus 2 (SARS-CoV2). At the time of writing 1st October 2020) there were more than 34 million confirmed cases worldwide with over 1,000,000 deaths^1^. Healthcare professionals (HCPs) are at higher risk of developing life-threatening infectious diseases through exposure to respiratory droplets, aerosols, and contact with patients’ blood or body fluids. This has also been demonstrated in previous epidemics such as the Ebola virus disease in 2014 and Severe Acute Respiratory Syndrome (SARS) a decade earlier, which were associated with very high fatality rates in HCPs (Styra et al., 2008; Forrester et al., 2014; Alfaraj et al., 2018). Whilst efforts to minimize the physical impact of infectious outbreaks take precedence, the potential mental health impact of such pandemics in the short-term and beyond should not be neglected (Barello et al., 2020; Galli et al., 2020; Siddiqui et al., 2021).

Previous studies conducted on the mental health impact of infectious outbreaks have found significant burden among healthcare workers and the general public. During the SARS outbreak, healthcare workers in a Beijing hospital who were quarantined, worked in a high-risk clinical setting or had family or friends infected with SARS, reported substantially more post-traumatic stress symptoms compared to those without (Xiang et al., 2020).

Increased exposure and unprecedented large-scale quarantine measures have a negative mental health impact on the public, in addition to the already tangible economic repercussions (Thompson, 2020; Weiss and Murdoch, 2020). Increased workload alongside a suboptimal working environment of inadequate personal protection equipment (PPE), risk of nosocomial transmission and constant changes in work structure can have detrimental effects on the mental wellbeing of HCPs. The need to isolate for fear of infecting friends and relatives results in loss of a social support network, further compromising the psychological resilience of HCPs.

Several studies exploring mental health impact of the current COVID-19 pandemic and risk factors for this have since been performed (Kisely et al., 2020). Whilst some individual studies have suggested an increased anxiety and risk of mental health problems in HCPs compared to non-HCPs (Zhang et al., 2020), subsequent meta-analyses have found a similar prevalence of anxiety and depression between healthcare workers and healthy controls from the general public (Krishnamoorthy et al., 2020; Luo et al., 2020; Pappa et al., 2020).

This observation can, in part, be explained by the different roles of HCPs. A study by Lu et al. (2020) demonstrated higher levels of psychological distress in HCPs working in hospital, compared to administrative staff. Work-related risk factors including close contact with infected patients, level of work experience and organizational support provided have also been shown to impact the psychological effect of emerging virus outbreaks (Kisely et al., 2020). These effects may be more prominent in junior or trainee doctors likely due to having to work in unfamiliar environment, with disrupted training and variable supervision (Kisely et al., 2020).

Healthcare professionals work under different schedules, including regular office hours, shift work, and swing shifts. Shift work and stressful work-related situations have been linked to poor mental health (Torquati et al., 2019). There is an established body of literature that has demonstrated the prevalence among physicians of a range of sleep-related issues, substance use and mental health disorders (Mihailescu and Neiterman, 2019; Petrie et al., 2019). These problems increase the risk of burnout or errors on the job. In those with pre-existing mental health disorders, there may be increased psychosocial problems, an increased risk of suicidal behavior, increased alcohol, or other psychoactive substance use, or a more severe form of the viral illness (Possamai, 2007; Greenberg et al., 2020).

Of note, most of these studies have evaluated only the immediate psychological impact of COVID-19 on HCPs and the general public. Moving forward, it is vital we identify the at-risk population and pre-disposing factors to higher psychological distress in order to design and target effective interventions to minimize the mental health impact of COVID-19. In the CoPE-HCP study, we aim to study the early and mid-term impact on mental and physical wellbeing in different cohorts of HCPs compared to the general population.

## Study Objectives

### Primary Objective

(1)To evaluate the prevalence of symptoms of anxiety and depression at the time of COVID-19 pandemic amongst HCPs in direct patient-facing roles, as compared to colleagues/participants in non-patient facing roles.(2)To determine the change in symptoms of anxiety and depression during the follow-up period amongst HCPs in direct patient-facing roles, as compared to colleagues/participants in non-patient facing roles.(3)To evaluate the change in proportion of those with suspected or confirmed COVID-19 during follow-up period amongst HCPs in direct patient-facing roles, as compared to colleagues/participants in non-patient facing roles.

### Secondary Objective

(1)To assess the impact of COVID-19 pandemic on symptoms of anxiety and depression and behavioral changes in HCPs in comparison to the non-HCPs at baseline and follow-up.(2)To assess the impact of COVID-19 related symptoms of anxiety and depression and behavioral changes on the subsequent physical wellbeing and absence from work due to illness.(3)To study the relationship of perceived stressors, such as PPE provision, work hours, future vaccine introduction, staffing levels and support at work, on the physical and mental health of HCPs.(4)To compare the differences in the prevalence of symptoms of anxiety and depression and behavioral changes, if any, by role and years of experience of HCPs.(5)To assess the impact of COVID-19 pandemic on the symptoms of anxiety and depression and behavioral changes of HCPs in the United Kingdom compared with HCPs in Europe, Asia, Africa, America, and Australasia.

## Methodology

### Study Design

An observational cross-sectional survey and cohort study design. A minimum of 1050 participants will be enrolled (minimum of 800 HCPs and 250 controls). Figure 1 shows the summary of the study scheme. The study recruitment was initiated on the 24th July 2020, just after the first peak of the pandemic (particularly in the United Kingdom and Western Europe), following formal ethical approval. The study is conducted as an online survey and can be complete by participants globally (see Supplementary Data Sheet 1 for questionnaire). The study is designed in London, United Kingdom and we envisage that as a consequence a large proportion of the participants will be from this region.

**FIGURE 1 F1:**
[figure not shown]
Study protocol flow diagram.

### Participant Selection

This is an international multicentric study enrolling three groups of participants.

#### Group 1

Healthcare professionals in direct contact with patients confirmed or suspected as having COVID-19 (*n* > 800).

Participants providing consent will be recruited for the follow-up questionnaire study (Group 4).

#### Group 2

Healthcare professionals in non-patient facing roles, not directly in contact with patients confirmed or suspected as having COVID-19 (*n* = 125, internal HCP control).

Participants providing consent will be recruited for the follow-up questionnaire study (Group 5).

#### Group 3

Non-Healthcare academic and research staff of Queen Mary University of London, and other professionals not working with patients confirmed or suspected as having COVID-19 (*n* = 125, population control).

Participants providing consent will be recruited for the follow-up questionnaire study (Group 6).

### Inclusion Criteria

(1)Aged ≥18 years(2)Electronic consent given(3)Belonging to one to the following groups:(a)HCPs with direct patient facing roles(b)Healthcare staff with no direct patient contact(c)Non-healthcare academic staff with no direct patient contact

### Exclusion Criteria

(1)Those who are not able to understand written English will be excluded by the design and methodology of the study, as the study invitation and all other information is provided in English.

#### Study Time Points

The study questionnaire will be conducted at baseline, after 6-weeks and 4-months for follow-up. The COVID pandemic in the United Kingdom started in March 2020 and the initial survey therefore assesses the early phase (baseline) and the follow-up (after 6-weeks and 4-months) questionnaires assess the mid-term impact.

##### Baseline

Recruitment will be open for approximately 6-weeks, starting from launch study date (24th July 2020).

##### Follow-up study

All participants consenting for follow-up will be sent further questionnaires after 6-weeks (up to 8-weeks) and 4-months (up to 6-months), from date of completion of the baseline questionnaire, to assess for change from baseline. To improve the uptake, we will also send weekly reminders (no more than 3) to those who have not completed the survey at first request. We expect that about 60% from each of the three baseline groups will agree to take part in the follow-up study, and about two-third of those will respond to the follow-up surveys.

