### Endpoints

#### Primary Endpoints

(1)Prevalence of anxiety and/or depression at baseline.(2)Change in prevalence of combined anxiety and depression from baseline.(3)Change in proportion of those who report signs and symptoms, or evidence consistent with COVID-19 from baseline to the end of study.

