#### Secondary Endpoints:

(1)Prevalence of combined anxiety, depression, or sleep disorder at baseline.(2)Prevalence of those with sleep disorders at baseline.(3)Change in prevalence of anxiety, depression, and sleep disorder from baseline to the two follow-up time points.(4)Change in prevalence of burnout from baseline to the two follow-up time points.(5)Proportion of those with low mental wellbeing at baseline and follow-up.(6)Change in behavioral habits such as smoking and alcohol intake from baseline to follow-up.(7)Proportion of those who report suspected or confirmed diagnosis of COVID-19.(8)Proportion of those who report their working conditions adversely affecting their personal relationships.

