### Method of Analysis

We will use the STATA 15 statistical software for analysis. Chi-square test will be used to compare the difference in prevalence of anxiety, depression and other variables between the groups at baseline. We will evaluate for changes in proportion of those outcomes at baseline to the end of the study using paired McNemar test. We will use logistic regression to assess the factors at baseline related to development of physical symptoms, overall, and in the HCPs group alone. Data will be described using appropriate descriptive statistics.

We will collect information for potential confounding factors such as age, gender, education level, and health conditions from both HCPs and their controls and adjust for these in the analysis. For all validated tools, we will use appropriate and previously published cut-offs to categorize them. For example, for the primary end point of anxiety, we will use the cut-off related to moderate anxiety, but also do a sensitivity analysis using cut-off using “mild” anxiety definition. Similar and consistent strategy will be followed for other validated tools. We will perform logistic regression for binary outcomes, such as those listed in our primary and secondary outcomes, after adjusting for pre-defined confounders including age, gender, and years of education. The choice of these *a priori* confounder is based on the significant association that exists for most of the study outcomes. We have also adjusted for time since the self-identified peak of the pandemic as this will impact on outcomes such as anxiety and depression. However, for the outcome of developing COVID-19 infection and change in prevalence of COVID-19 infection, we will also adjust for pre-existing medical conditions.

We will also stratify HCPs according to their roles (doctors, nurses, pharmacists, healthcare assistants etc.), and will evaluate and compare the endpoints by respective roles. Comparison between HCPs from the United Kingdom and outside will be undertaken adjusting for the self-identified peak of the pandemic in that region. We also will assess whether the years of experience (as a categorical variable) has any impact on the measured outcomes.

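### The last survey may fall 4 to 6 months after baseline, but the covariates named for the COVID-19 outcome do not include length of follow-up

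*Protocol article*

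**What the plan says.** **Timing.** The Follow-up study section sets the later questionnaires at "after 6-weeks (up to 8-weeks) and 4-months (up to 6-months), from date of completion of the baseline questionnaire". On reminders it says that "we will also send weekly reminders (no more than 3) to those who have not completed the survey at first request". Both rules apply to all groups alike.

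**Outcome.** Primary objective 3 is "To evaluate the change in proportion of those with suspected or confirmed COVID-19 during follow-up period amongst HCPs in direct patient-facing roles", compared with colleagues or participants in non-patient-facing roles. Primary endpoint 3 is "Change in proportion of those who report signs and symptoms, or evidence consistent with COVID-19 from baseline to the end of study". Secondary endpoint 7 is "Proportion of those who report suspected or confirmed diagnosis of COVID-19", with no time frame. The Physical Health definition is self-reported: symptoms together with either a positive test or self-isolation of at least 7 days. It gives no recall period.

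**Analysis.** Under Method of Analysis, "We will evaluate for changes in proportion of those outcomes at baseline to the end of the study using paired McNemar test". Binary outcomes go into logistic regression "after adjusting for pre-defined confounders including age, gender, and years of education". The article also adjusts for time since the peak of the pandemic as identified by the participant, citing its effect on outcomes such as anxiety and depression. One addition is specific to COVID-19: "for the outcome of developing COVID-19 infection and change in prevalence of COVID-19 infection, we will also adjust for pre-existing medical conditions". Length of follow-up is not named, and neither is a rate or time-to-event method.

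**The concern.** Whether someone has developed COVID-19 since baseline is a cumulative question, and the chance of a yes grows with the time covered. If one person answers at 4 months and another at 6, the second has had half as much time again in which to be infected. A binary model without a term for that interval counts both reports as the same observation.

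Differences between individuals mainly add noise. They become bias in primary objective 3 if the interval is also related to group, because a later-answering group then looks more infected at an identical infection rate. McNemar's test takes no covariates, so the within-person change also reflects whatever mix of intervals happened to occur.

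The article does tailor the adjustment set to this outcome by adding pre-existing conditions. The most direct determinant of a cumulative proportion, the time over which it accumulates, is not in the set.

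**Working it through.** The article gives no figure for time at risk, so there is none to reproduce.

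**1. Spread between individuals.** From the stated window, 6 / 4 = 1.50, so the longest interval is 50% longer than the shortest. If every request goes out at exactly 4 months (4 × 30.44 = 121.8 days) and replies stop 3 to 4 weeks later, after the last of three weekly reminders, the ratio is (121.8 + 21)/121.8 = 1.17 to (121.8 + 28)/121.8 = 1.23. The practical spread may thus be 17% to 23%. The text does not settle whether the 6-month limit applies to sending or to completion.

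**2. Effect on a cumulative proportion.** Assume a constant monthly rate r, equal in all groups, with reports covering the time since baseline: p(t) = 1 − exp(−r·t).

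At r = 0.02 (assumption), p(4) = 1 − exp(−0.08) = 7.7% and p(6) = 1 − exp(−0.12) = 11.3%, a ratio of 1.47. This contrasts two individuals at the ends of the window.

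**3. Effect of a gap in group means.** Take one group at 4.3 months on average and the other later by the stated gap (both assumed; 1 week = 7/30.44 = 0.23 month). The table gives the spurious difference in percentage points.

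| Rate per month (assumed) | Gap 1 week | Gap 2 weeks | Gap 1 month |
|---|---|---|---|
| 1% | 0.2 | 0.4 | 1.0 |
| 2% | 0.4 | 0.8 | 1.8 |
| 4% | 0.8 | 1.5 | 3.3 |

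For example, at 2% and one month: [1 − exp(−0.02 × 5.3)] − [1 − exp(−0.02 × 4.3)] = 10.1% − 8.2% = 1.8 points from unrounded values, a relative risk of 1.22.

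**4. Effect on the test.** The article expects 60% to agree to follow-up and two-thirds of those to respond: 0.60 × 2/3 = 40%. That is about 320 of the minimum 800 and 100 of the 250 controls. As a deliberately high-risk illustration, borrow the 20% that the Sample Size section uses for physical symptoms as the 4-month risk, so that p(t) = 1 − 0.8^(t/4). Put the 320 at the later time and the 100 at 4 months. The rejection probability of a two-sided 0.05 two-proportion test with equal infection rates is then:

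- gap of a quarter month (about 1 week): 21.1% v 20%, 0.054
- gap of half a month (about 2 weeks): 22.2% v 20%, 0.070
- gap of 1 month: 24.3% v 20%, 0.136

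**5. Does time since peak stand in for the interval?** It locates a response in the epidemic. Two people answering on the same day in the same region share it, yet their intervals differ if they joined at different points of the roughly 6-week recruitment period. If it is recorded only at baseline, it carries no information on when the last survey was answered. The text does not say when it is measured.

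**The case against.** The strongest objection is that the recall period is not visible. The COVID-19 items are customised questions in Supplementary Data Sheet 1, which is not shown. They may use a fixed recall period or already ask for onset or test dates. The article also speaks of change in prevalence as well as of developing infection, so a purely cumulative outcome is not certain. This stands: a fixed recall period would remove most of the problem, and the sizes above are conditional on reports covering the time since baseline.

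A reader might infer that time at risk could differ by 50% between groups, or that overworked patient-facing staff will answer later. The documents support neither. The first would need every member of one group to answer at 4 months and every member of the other at 6, although window and reminder rule are common to all. The second is conjecture. With only three weekly reminders, a one-month gap in means is hard to reach, and at gaps of 1 to 2 weeks the test stays close to its nominal level. The differences are also small beside the roughly 12 points for which the follow-up is powered.

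Nor is it right that COVID-19 is compared only as a crude proportion. Adjusted logistic regression is planned, time since peak covers epidemic phase in part, and the confounder list is worded so that it is not closed.

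Finally, visit windows and offsets are often left to an analysis plan. Here, however, the article itself states the window, the endpoint, the tests and a covariate specific to COVID-19. The point concerns how these stated choices combine.

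**Conclusion.** The point holds in limited form. As written, the article combines a 4-to-6-month window with a binary COVID-19 outcome and names no adjustment for the interval. Time at risk can differ by up to 50% between individuals, or about 17% to 23% if requests go out at 4 months and replies end with the reminders. Between groups the difference is smaller and unknown.

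The resulting bias in primary objective 3 is probably modest: under one point for a mean gap of up to 2 weeks at 2% per month, and 1.8 points for one month. This rests on an assumed constant and equal infection rate, assumed gaps, and reports that cover the time since baseline. It is an inexpensive improvement to the analysis of a primary endpoint, not evidence that the group comparison is distorted.

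**What to change.** In the Method of Analysis model for developing COVID-19, include the interval from baseline completion to final-survey completion, either as a log-interval covariate in the logistic model or as a log-interval offset in a complementary log-log model. Report the distribution of intervals by group, and state the recall period of the COVID-19 items.

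If onset or test dates are already collected, add a sensitivity analysis limited to events within 4 months of baseline. A new survey item is not needed: the article is dated October 2020, when follow-up from a July 2020 launch was already due, and ethics approval covers the written participant material. Cutting the primary count at 4 months is not needed either.

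The cost is one model term and one descriptive table. Follow-up is timed from baseline completion, so those dates must be held; completion dates of the later surveys should be available from the web survey platform.
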